#### Trial design

This study adopts a prospective, assessor-blinded, randomised controlled trial with fractional factorial design by using the MOST principles to evaluate the effects of the five individual components and their two-way interactions (including self-care skills, behavioural problem management, behavioural activation, mindfulness yoga and support group; Table 1). A complete factorial experiment of the five factors would have 2^5^ = 32 experimental conditions (ECs). To conserve resources and reduce logistical complexity, we select a 25–1 fractional factorial design and decrease the number of ECs from 32 to 16 [20]. Our fractional factorial design is made up of a strategically selected subset of 32 ECs based on prioritising the estimation of intervention component main effects and two-way interactions [21]. All the included ECs are listed in Table 1. The study contains a subset of ECs, so the participants will not be randomised into a usual care/control group but every EC can be served as a control condition under different circumstances to test the effect of each component. For example, the effect of component 2 on primary outcomes could be examined through the comparison of participants in EC1 to EC8 and those in EC9 to EC16. In addition, the study assumes the presence of overlapping components within the 16 ECs. These overlaps will be recognised and carefully measured through fidelity monitoring. This study will conform with the Declaration of Helsinki.

**Table 1 Tab1:** Experimental conditions of the fractional factorial RCT

	Component					
Experimental condition	1	2	3	4	5	6
1	Yes	Yes	Yes	Yes	Yes	Yes
2	Yes	Yes	Yes	Yes	No	No
3	Yes	Yes	Yes	No	Yes	No
4	Yes	Yes	Yes	No	No	Yes
5	Yes	Yes	No	Yes	Yes	No
6	Yes	Yes	No	Yes	No	Yes
7	Yes	Yes	No	No	Yes	Yes
8	Yes	Yes	No	No	No	No
9	Yes	No	Yes	Yes	Yes	No
10	Yes	No	Yes	Yes	No	Yes
11	Yes	No	Yes	No	Yes	Yes
12	Yes	No	Yes	No	No	No
13	Yes	No	No	Yes	Yes	Yes
14	Yes	No	No	Yes	No	No
15	Yes	No	No	No	Yes	No
16	Yes	No	No	No	No	Yes

### Methods: participants, interventions and outcomes

#### Study participants

Eligible family caregivers will be recruited if they satisfy the following inclusion criteria: (i) Hong Kong Chinese citizens aged 18 years or above; (ii) spouse, adult child or child-in-law of a care recipient; (iii) without cognitive impairment (i.e. HK-MoCA 5-Min with a cut-off score that is respective to the age and educational level); (iv) primary family caregiver for an individual with dementia (at least 20 h per week) for at least 1 year; individuals are considered as caregivers if they have assisted with the activities of daily living (ADLs) and instrumental activities of daily living (IADLs) of people with dementia; and (v) caregivers with a certain degree of depression or feeling of burden (Patient Health Questionnaire-9 > 9 or Zarit Burden Scale > 18) to ensure a homogeneous sample [22, 23].

#### Study setting, sampling and recruitment strategies

We will reach potential participants by using traditional and social-networking recruitment strategies. Traditional methods include newspaper and radio advertisements as well as referrals made through psychiatric and psychogeriatric clinics, non-governmental organisations providing elderly community services, Alzheimer’s associations and university campuses. Social-networking methods include regular postings on sites, such as Facebook, and contextual targeting methods for identifying and directly targeting potential participants (based on their social media comments) with recruitment advertisements.

#### Allocation concealment, assignment of interventions and blinding

After baseline assessment, all participants will receive component 1 (dementia and caregiver education) as the core intervention. Participants will be randomly assigned to one of the 16 ECs (Table 1) by using the fractional factorial MOST design. Computer-generated random numbers will be used for allocation. Participants will be informed of their assigned group by an independent person not involved in the assessment. The allocation list will be computer-generated by an independent researcher and concealed from other researchers and participants until the time of assignment. Outcome assessors will be blinded to participant group allocation. Unblinding should only occur for participant safety concern when a series adverse event transpires and knowledge of the assignment of intervention could mitigate the health risk (Fig. 1) [24].

**Fig. 1 Fig1:**
[figure not shown]
SPIRIT figure — schedule of enrolment, interventions, and assessments

#### Components of the multicomponent intervention

In the MOST preparation phase, we develop a conceptual model (Fig. 2) based on the theoretical framework model for the stress-health process of informal caregivers for PWDs [25]. Figure 3 illustrates how each individual component affects its proximal outcome, which in turn affects the primary outcome.

**Fig. 2 Fig2:**
[figure not shown]
Supposed impact of the different intervention components on the stress-health process of the informal caregiver (adapted from Schulz [25])

**Fig. 3 Fig3:**
[figure not shown]
Mechanism of the multicomponent intervention

*Component 1: dementia and caregiving education.* This core component will provide general knowledge about dementia, information on skills for communicating with PWDs, and common problems related to caregiving and seeking help. In line with the methods employed by Kwok [26], three 30-min sessions will be delivered via telephone and information will be provided in the form of presentation slides (also available in audio and video formats). Following safety walkthroughs (via Zoom) during the first two sessions, advice will be offered about ensuring home safety (e.g. through home modifications).

*Component 2: self-care skills.* Participants will receive information related to the importance of self-care and its associated skills. This information will be provided in the form of presentation slides (also available in audio and video formats). Caregivers will be reminded of the importance of maintaining good health and continuing healthy behaviour for themselves and their care recipients. They will also be taught to use health passports to keep records of health conditions and doctor appointments of themselves and their care recipients.

*Component 3: behavioural symptom management.* This component is adopted from previous studies conducted by our team members [27, 28], which will be delivered via telephone by well-trained research assistants. The antecedents–behaviour–consequence model [29] will be introduced to caregivers to manage the behavioural symptoms of care recipients. They will be taught to observe and record the antecedents and consequences of problem behaviour and to use weekly records to keep track of behavioural changes. They will also be taught how to develop plans to change precipitating events or their reactions to these problem behaviours. Home practices will be introduced, and caregivers will be encouraged to complete them regularly.

*Component 4: behavioural activation.* In this component, we will encourage participants to schedule their engagement in pleasant activities into their daily routines by following the telephone-based protocol used in previous studies of Chinese caregivers conducted by our team members [27, 28]. Specifically, caregivers will learn about the principles of BA and participate in sessions on activity monitoring, activity scheduling, reinforcing or modifying a pleasant event and activity rescheduling based on changes after modification.

*Component 5: modified mindfulness-based cognitive therapy.* The programme will be led by a mindfulness practitioner and consists of seven 2-h group sessions to be delivered online via video-conferencing software. Each session will have a theme and related activities. For instance, in the first session, the theme is waking up from automatic pilot and participants will be required to scan their body and perform raisin-eating meditation.

*Component 6: support group.* This component consists of six 1-h group sessions delivered online, in which six major themes will be covered [30]: introduction of dementia caregiving and development of a mutual support group; improvement of home care skills and interpersonal relationships; awareness of caregivers’ mental health; reaching out to community resources; experience sharing on behavioural symptom management; and conclusion and review. These sessions will involve sharing information and engaging participants in group discussion as well as the provision of psychological support and participation in problem-solving exercises. An experienced social worker will act as a facilitator, and two peer leaders will be elected by group members.

#### Outcome measures

All outcome measures have been validated in local context and will be used in participants. Figure 3 lists all the primary and proximal outcomes.

#### Primary outcome measures

*Physical health status* will be measured by the validated 12-item Short-Form Health Survey (SF-12) [31]. SF-12 consists of eight domains, and the participant’s health condition is rated on a 4-point Likert scale. Only the self-rated and physical component will be used to measure the primary outcome, and a high score indicates a good health condition. The Cronbach’s alpha of the physical component in the Chinese version is 0.68 [32].

*Caregiver burden and general stress* will be measured by the 12-item Zarit Burden Interview scale (ZBI) [33] and the 10-item Perceived Stress Scale (PSS) [34]. ZBI uses a 5-point Likert scale, and a high score indicates a high caregiver burden. The Cronbach’s alpha of the validated Chinese version is 0.84 [33]. PSS consists of the positive element and negative element subscale and measures the subjective perception of stress in a 5-point Likert scale. A high score indicates a high stress level. The Cronbach’s alpha is 0.75 (0.82 for negative subscales; 0.87 for positive subscales) [35].

*Psychological well-being* will be measured by the four subscales in Ryff’s Psychological Well-Being Scale in 24-item version [36]: self-acceptance (4 items), positive relations to others (4 items), purpose in life (4 items) and personal growth (4 items). The 16 items of subjective psychological well-being will be measured on a 6-point Likert scale. The Cronbach's alpha of the four subscales ranges from 0.77 to 0.88 [36].

*Anxiety and depressive symptoms* will be measured by the 7-item Chinese version of the Anxiety Subscale of Hospital Anxiety and Depression Scale (HADS-A) [37] and the 9-item Chinese version of the Patient Health Questionnaire (PHQ-9), respectively [22]. HADS-A uses a 4-point Likert scale to measure anxiety symptoms over the past week. The Cronbach’s alpha is 0.77 for the anxiety subscale. PHQ-9 uses a 4-point Likert scale to assess depressive symptoms over the past week [38]. A high score indicates severe depressive symptoms. The Cronbach’s alpha is 0.91 [39].

*Perceived adequacy of functional social support* will be measured by the 20-item Medical Outcomes Study Social Support Survey (MOS-SSS) [40]. MOS-SSS measures function aspects of perceived social support in four domains by using a 5-point Likert scale: tangible support, emotional-information support, positive social interactions and affectionate support. The Cronbach’s alpha of the overall scale is 0.98 [41].

#### Proximal outcomes

*Self-care* will be measured by the 14-item self-care subscale in Risk Appraisal Measure (RAM-SC) [42, 43]. The subscale illustrates the unique risk profile of caregivers in terms of self-care. A high score indicates a low risk of caregivers.

*Caregiving strategies* will be measured by the 34-item Dementia Management Strategies Scale (DMSS) [42, 43]. The scale uses a 5-point Likert scale and consists of three domains, namely, criticism, encouragement and active management. The Cronbach’s alpha of the three subscales ranges from 0.86 to 0.90 [42, 43].

*Engagement in pleasurable activities* will be measured by recording the frequency (times per week) and duration (minutes in each time) of each engagement in the past 2 weeks.

*Mindfulness* will be measured by the 20-item version of the Five Facet Mindfulness Questionnaire (FFMQ) [44]. Using a 5-point Likert scale, it measures five facets of mindfulness, namely, observing (4 items), describing (4 items), acting with awareness (4 items), nonjudging to inner experience (4 items) and non-reacting to inner experience (4 items). A high score reflects a high level of mindfulness. The Cronbach’s alpha values are 0.83 in the community sample and 0.80 in the clinical sample [44].

*Social support* will be measured by the 12-item Multidimensional Scale of Perceived Social Support (MSPSS) [45]. The scale uses a 7-point Likert scale and consists of three sources of support: family, friends and significant other. The Cronbach’s alpha of the three subscales ranges from 0.85 to 0.91. [46].

*Satisfaction with the support group* will be measured on a 7-item scale during the post-intervention. Participants will report their satisfaction with specific components and quality of service [46].

#### Moderators (control variables)

*Positive caregiving appraisal* will be measured by the 11-item Positive Aspect of Caregiving (PAC) [47]. The two domains, namely, enriching life and affirming self, are measured on a 5-point Likert scale. The Cronbach’s alpha is 0.89.

*Caregiving self-efficacy* will be measured by the 15-item Revised Scale of Caregiving Self-Efficacy [48]. The scale measures caregiving self-efficacy in three domains: obtaining respite, managing disruptive patient behaviour and controlling upsetting thoughts. Participants will be asked to rate their confidence level on a continuous scale from 0 to 100% for each item. A high score indicates high confidence in carrying out caregiving tasks. The Cronbach’s alpha for the three subscales ranges from 0.89 to 0.90 [49].

*Health behaviour* will be measured by the 6-items of self-designed statements that describe the frequency of engaging in health behaviour in the past 1 month by using a 4-point Likert scale. A high score indicates a high level of frequency in engaging health behaviour.

#### Monitoring

Since this is a low-risk intervention, which aims to support caregivers’ wellness via psychosocial and behavioural techniques, no data monitoring committee is needed. There are no specific criteria for discontinuing or modifying assigned interventions, and there will be no interim analyses or predefined stopping guidelines. Participants have the freedom to discontinue their involvement in the study at any time and for any reason, as outlined in the informed consent documents. Serious adverse events and other harms from the intervention are not anticipated as this is a low-risk intervention to promote caregivers’ wellness. If participants experience any potential adverse events (such as anxiety, depressed mood) related to their participation, they will be reminded to promptly inform the research team. Adverse event, if applicable, will be promptly reported to the trial supervisor ([name]) and to the ethics committee. The trial supervisor and ethics committee will review the adverse event to determine if any action, including terminating the trial, is necessary. An independent ethics committee, separate from the sponsor, will receive an annual report on the trial’s conduct, whilst the sponsor will review an annual progress report on the trial's progress.

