## Main paper

### Introduction

Dementia is an impending healthcare crisis that affects more than 55 million individuals worldwide. With the ageing population, this number is expected to reach approximately 78 million by 2030 and 139 million by 2050 [1]. The global financial burden of dementia is estimated to be USD 1.3 trillion and may reach USD 2.8 trillion by 2030. Dementia is a progressively degenerating disease that causes multiple cognitive deterioration, which results in disability, dependence, institutionalisation and mortality. Long-term care of patients with dementia is mostly provided by family caregivers, who provide unpaid or informal attention and play an essential role for the persons they are taking care of and for the overall healthcare system. Family dementia caregivers are more stressed, suffer more serious anxiety and depressive symptoms and are at higher risk of cardiovascular diseases than non-dementia caregivers [2]. These over-burdened caregivers are more likely to give up their caregiver role by institutionalisation of their care recipient [3]. All of these factors are projected to significantly increase the costs of healthcare and long-term care in the future. Therefore, effective interventions should be designed to reduce the negative effects of caregiving on family dementia caregivers.

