#### Treatment fidelity

As shown in Table 1, two to six components will be delivered to participants, and the selected components in each experimental condition will be integrated seamlessly. The intervention will be administered through telephone/video-conferencing software (i.e. Zoom) by well-trained research assistants. Research assistants will be provided with 10 h of intensive training, which will include reading materials, structured role play and practice opportunities for each component. Under experimental condition 1, in which participants will receive six components, the intervention will consist of 16 weekly sessions of approximately 45 min each as well as three booster support group sessions that will take place at 1, 2 and 4 months after the completion of the intervention. The intervention will be completed in 6 weeks under experimental conditions 8, 12, 14, 15 and 16, in which participants will receive only two components.

To ensure treatment fidelity, interventionists will submit an audiotape of their first implementation of a component session for review and receive feedback from the research team. We will monitor and maintain intervention implementation through weekly supervision meetings and monthly conference calls, which will involve all interventionists. Interventionists will also submit taped intervention sessions throughout the study, and the research team will review at least 20% of the recordings. In addition, a delivery assessment form will be completed after each contact with a caregiver, and the research team will review the forms to ensure adherence to the intervention protocol.

Furthermore, interventionists will use the intervention fidelity form to record the number and duration of home visits, telephone calls and sessions. Interventionists will also rate caregivers’ enactment in four aspects: data collection, home assignments, use of notebooks and use of written prescriptions [50]. A satisfaction questionnaire will be conducted after the intervention to collect information about participants’ satisfaction with specific components and with the quality of services [46].

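### Participants are asked to report anxiety or depressed mood only if they think it is related to taking part, so events they put down to caregiving may never reach those who review safety

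*Protocol article*

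**What the plan says.** The Monitoring section gives the instruction on when participants should contact the team: "If participants experience any potential adverse events (such as anxiety, depressed mood) related to their participation, they will be reminded to promptly inform". Adverse events then go to the trial supervisor and the ethics committee, with this task: "The trial supervisor and ethics committee will review the adverse event to determine if any action, including terminating the trial, is necessary". The same section states that there is no data monitoring committee, no interim analysis and no predefined stopping guideline, on the ground that the intervention is low-risk.

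The Introduction describes the population: "Family dementia caregivers are more stressed, suffer more serious anxiety and depressive symptoms" than other caregivers. Study participants makes one of two scores a condition of entry: "caregivers with a certain degree of depression or feeling of burden (Patient Health Questionnaire-9 > 9 or Zarit Burden Scale > 18". Under Primary outcome measures, anxiety (HADS-A) and depressive symptoms (PHQ-9) are measured in every participant. Data collection procedures sets these assessments at baseline (T0), 6 months (T1) and 12 months (T2).

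**The concern.** Sound practice is to collect adverse events whatever their presumed cause and to judge relatedness afterwards, by someone other than the participant. The Monitoring wording reverses that order for the two events it names.

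In this population the order matters. Anxiety and low mood are what dementia caregiving itself is expected to produce, and entry requires raised depressive symptoms or raised burden. A caregiver whose mood worsens during the trial can reasonably blame caregiving and, following the instruction as written, say nothing. With no monitoring committee, the supervisor and ethics committee depend on what reaches the team. Reported counts would then partly reflect participants' own attributions. At stake are prompt review of individual participants and the completeness of the harms report. The efficacy analysis is not affected.

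**Working it through.** The point rests on wording, so the main check sets the relevant sections side by side.

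1. **Reporting instruction (Monitoring).** The condition of being related to participation is attached to what participants are reminded to report. Calling the events potential softens this a little but does not remove the condition.
2. **What follows (Monitoring).** The supervisor and ethics committee act on events that have been reported. Nothing in the section widens what participants are asked to report.
3. **Other mentions of adverse events.** Allocation concealment, assignment of interventions and blinding mentions them only as a reason for unblinding.
4. **Other contact records (Treatment fidelity).** A delivery form is completed after each contact, but its stated purpose is different: "the research team will review the forms to ensure adherence to the intervention protocol". Weekly supervision meetings are listed for maintaining implementation. Neither is described as a way of recording harms.
5. **Symptom scores.** PHQ-9 and HADS-A are collected from everyone regardless of cause. After entry, the only use the article states for them is outcome analysis.
6. **Rival explanation.** The Introduction and the entry criteria together make caregiving an obvious alternative cause. Entry is by depression *or* burden, so not every participant starts with depressive symptoms, but all start with one or the other.

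**Can the number of missed events be estimated?** Only under assumptions that the documents do not supply. Take 200 assessed (the sample after attrition in Sample size estimation), a T0-to-visit correlation r of 0.5 to 0.7, worsening of at least 1.5 SD on PHQ-9 as the event, and 25% to 75% of those affected blaming caregiving. The last three are assumptions. The standard deviation of change, in baseline SD units, is √(2(1 − r)): 1.00 at r = 0.5 and 0.775 at r = 0.7.

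- *No average change.* z = 1.5/1.00 = 1.50 gives 6.68%, or 13.4 of 200. z = 1.5/0.775 = 1.94 gives 2.64%, or 5.3 of 200. Not asked to report: 0.25 × 5.3 = 1.3 up to 0.75 × 13.4 = 10.0 per visit.
- *Average improvement of 0.60 SD.* This is the pre-post effect cited in Sample size estimation, where the outcome is not named. z = 2.1/1.00 = 2.10 gives 1.79%, or 3.6 of 200. z = 2.1/0.775 = 2.71 gives 0.34%, or 0.7 of 200. Not asked to report: 0.25 × 0.7 = 0.2 up to 0.75 × 3.6 = 2.7 per visit.

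The result runs from about 0.2 to 10 per visit, driven by the assumed inputs. It also counts ordinary fluctuation in mood, which is not harm. It shows that no usable figure can be given.

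**How much could still change?** Trial status gives the end of recruitment as 31 December 2022 and registration as 9 May 2023. Treatment fidelity gives the longest course as 16 weekly sessions. If the last participant started at once, 31 December 2022 + 16 × 7 = 112 days is 22 April 2023, before registration. Only booster support group sessions, at 1, 2 and 4 months after completion, and follow-up visits to 30 November 2023 would remain.

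**The case against.** The strongest reply is that a single summary sentence in a condensed article is being read as an operating rule. The next sentence sends adverse events to the supervisor without limiting them to those the participant thinks related. Staff are in repeated contact with participants and meet weekly, so they may learn of events in other ways. The full protocol may describe how staff ask about events or respond to distress. This stands as a reason for restraint, and the absence of a distress procedure or score trigger is therefore not raised as an error. It does not rescue the sentence, which states a condition that a fuller document would have to override.

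A reader might infer that the wording takes a causality assessment away from the reviewers. The article does not support that: it asks the supervisor and ethics committee to decide on action and names no relatedness judgement. What holds is narrower: they cannot form any view on events they do not see.

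A reader might also infer that mood harm would go undetected. That is not so at group level. PHQ-9 and HADS-A are primary outcomes in everyone, analysed as component-by-time effects, and average worsening under a component would appear there whatever its perceived cause. What remains is prompt review of individuals.

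Nor does the disappointment with allocation foreseen under Limitations strengthen the case. The article links it to reduced motivation, and a caregiver upset by allocation would see it as related to participation and so be asked to report.

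**Conclusion.** The concern holds in a limited form. The stated instruction filters reports by the participant's own view of cause, no other intake route is stated, and the entry criteria make it plausible that some worsening mood is put down to caregiving and not reported. That rests on the text alone.

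The effect is minor: the intervention is low-risk, group-level worsening would be seen at T1 and T2, and most delivery was over by registration. It would be tempting to attach a count of missed harms, but the documents give neither the correlation nor the share of participants who would blame caregiving, so no count is claimed.

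**What to change.** In Monitoring, remove the relatedness condition. Suitable wording would be: *Participants will be asked to tell the research team about any anxiety, depressed mood or other adverse event, whatever they believe caused it.* The team records each event, and the supervisor and ethics committee form the view on relatedness. Where a report is made at an assessment visit, it should be passed on without reference to allocation, since "Outcome assessors will be blinded to participant group allocation".

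As an option, use the PHQ-9 and HADS-A scores already collected to report marked worsening from T0 descriptively, by component present v absent and without a test. Any cut-off should be left to the ethics committee. This partly makes up for events that new wording can no longer recover, though scores at 6 and 12 months show only late or persisting worsening.

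The cost is a short ethics amendment and some extra reports to review, part of which will reflect caregiving and not the intervention. No new measures or visits are needed.
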